### Implementation outcomes

Because the iLIVE intervention has high potential for scalability and, if proven efficacious, could help substantial numbers of men, the iLIVE trial was designed using a Hybrid Type I Implementation framework [16]. Select evaluation criteria proposed by Proctor et al. [37] informed data collection in the following intervention implementation areas: feasibility; cost; acceptability; adoption; appropriateness; fidelity; and sustainability.

As described under Secondary Outcomes, some measures serve as independent outcomes but also contribute to broader implementation domains. For example, safety is an important independent outcome, but, when evaluated along with process data gathered on intervention engagement (i.e., % of website sessions completed [obtained from website analytics], use of scales and Fitbits^®^ [obtained from Fitabase^®^], and class attendance logs), as well as retention from study tracking, the end result is a more comprehensive evaluation of feasibility. Likewise, health care utilization and QALYs and costs associated with intervention delivery will be used in a thorough cost-analysis to assess cost-effectiveness of the intervention. To evaluate other implementation domains, a combination of quantitative data (from recruitment or tracking databases, website or device analytics, or participant surveys), along with qualitative data (from semi-structured interviews with participant subsamples or stakeholders [health care providers and health system administrators]) provides a comprehensive approach to evaluate other domains. Examples are as follows.

#### Acceptability

Recruitment databases yield enrollment rates (total and in specific age, race/ethnicity, or residential subgroups) and percent refusals or ineligibles by reason, whereas semi-structured interviews among refusers and enrollees provide qualitative data on ways to improve future enrollment and retention. Acceptability also is assessed among providers and administrators.

#### Adoption

Recruitment databases yield sources of referral, tracking databases, or data from website or device analytics provide quantitative data on withdrawal and adherence, whereas semi-structured interviews among dropouts, health care providers, and health system administrators provide qualitative data on barriers/facilitators to referral or participation.

#### Appropriateness

Post-intervention surveys (at 6 months) query all participants on the relevance and fit of the interventions using quantitative means, whereas semi-structured interventions completed on a subset of participants provide more detail on suggestions for future programming. Interviews among providers and health system administrators delve into how iLIVE aligns with the extant mission and fits into existing services. 

#### Fidelity

Data from website or device analytics, as well as training logs and fidelity checklists provide quantitative data on intervention delivery, whereas semi-structured interviews among participants provide qualitative data on program quality and suggestions for improvement. 

#### Sustainability

All participants are encouraged to continue with interventions beyond 6-months and their engagement with websites, devices, and in the case of the experimental group continued exercise session attendance, is monitored from 6 to 12 months to gauge sustainability; semi-structured interviews with health care providers and health system administrators provide qualitative data to inform future integration with clinical care.

Semi-structured interviews are conducted over the telephone by trained moderators using interview guides tailored toward the patient subsample or type of stakeholder and using in-depth interviewing methods [38].

### Randomization and interventions

Upon completion of baseline data collection, participants are block randomized (size = 6) by timing of ADT (current vs. past). Randomization sequences are generated by the study biostatistician who has no contact with participants, and who then informs the study coordinator about assignment to the iLIVE intervention (iLIVE) or enhanced usual care (EUC) arms. Both arms receive an emailed “Welcome” message informing them of their status along with pertinent links to websites and equipment. Because self-monitoring is a key construct of behavior change [39, 40], both arms are encouraged to continue Fitbit^®^ and Aria^®^ scale use and use the open access resources available through MyFitnessPal, Inc. (https://www.myfitnesspal.com/). iLIVE is designed as an adjunct to standard care and not interfere with its delivery. The interventions and assessments are conducted exclusively via the internet.

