## Methods/design

### Design and settings

iLIVE is a 2-arm, single-blinded RCT that relies on a single Institutional Review Board Protocol administered by the OHSU Knight Cancer Institute (25281) with approval by UAB (300011042). Designed with the anticipation that, if found acceptable and effective, iLIVE could progress to future larger-scale implementation effectiveness trials, the RCT was designed under a Type I Hybrid Effectiveness-Implementation framework that simultaneously assesses intervention effectiveness and implementation factors [16]. iLIVE is registered on ClinicalTrials.gov (NCT06011499) and is being conducted throughout North America. Active solicitation via physician referral, patient portal prompts and letters of invitation with telephone follow-up are underway at OHSU (and through their liaison with the Oregon State Cancer Registry) and UAB, with nationwide outreach conducted through national and regional prostate cancer support groups, as well as a study website (https://ilive4health.org/welcome). Since all study activities occur online, men can be recruited from anywhere across the continent through various strategies, but all consenting is conducted electronically by the OHSU study team. Signed informed consent (in which the risks of dietary modification and physical activity are detailed, and participants acknowledge these risks and assume potential related-costs) is obtained from all trial enrollees prior to data collection via Adobesign^®^ (San Jose, CA); study ID numbers that assure that the collection of data is deidentified are assigned at that time.

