### Statistical analysis

#### Power and sample size calculation

The sample size requirements for this RCT were based on estimates obtained from an ongoing trial [36]. We estimated that 40% of men assigned to the iLIVE intervention vs. 10% of those assigned to usual care will demonstrate clinically significant improvements from baseline to 6-month follow-up in the obese frailty phenotype (defined as clinically significant weight loss of 5% and clinically meaningful change in 2 or more frailty components, i.e., weakness, slowness, fatigue, inactivity, and/or illness). However, we powered this trial to detect smaller effects that are likely still clinically meaningful. Assuming alpha=0.05 (two-tailed) and power=0.80, a sample size of 200 complete cases (100 in each group) would be required to detect proportional differences in the 18–20% range. Assuming an attrition rate of ~ 20%, the total sample size required is *N* = 250 (*n* = 125 in each group). If attrition is lower than expected, we will need to randomize fewer participants to achieve the desired sample size. Additionally, this sample size results in even more statistical precision when examining secondary outcomes that yield continuous data.

Sample sizes for the implementation analysis are based on estimates of achieving thematic saturation [55, 56]. Here, we anticipate interviewing 30 prostate cancer survivors (6 who refuse trial participation, 12 who enroll but drop out before the end of 6 months, and 12 who complete their 6-month assessment). Maximum variation sampling will be done based on study group allocation (enrollees only), age (< 75 vs. 75+) and region of the country (west vs. east). Plans also include interviewing eight oncology clinical care team members (different types of oncology providers and nurses) and eight health system administrators (Chief Executive Officers, etc.).

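### One published block size of 6 within two ADT strata lets anyone who tracks assignments deduce, on average, a quarter of allocations with certainty; varying the sizes is a cheap improvement

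*Protocol article*

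**What the plan says.** All references are to the protocol article.

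- **Randomization and interventions:** "participants are block randomized (size = 6) by timing of ADT (current vs. past"). No second block size and no random variation of size is mentioned.
- **Same section, who generates the list:** "Randomization sequences are generated by the study biostatistician who has no contact with participants", "who then informs the study coordinator about assignment to the iLIVE intervention (iLIVE) or enhanced usual care (EUC) arms".
- **Same section, timing:** randomization takes place "Upon completion of baseline data collection". Both arms are then told their status in a welcome email, so participants know their arm.
- **Design and settings:** "iLIVE is a 2-arm, single-blinded RCT". Blinding is stated for the outcome assessors (Measures) and for the team that classifies adverse events (Safety). None is stated for the coordinator.
- **Power and sample size calculation:** "the total sample size required is *N* = 250 (*n* = 125 in each group"), which implies 1:1 allocation and so 3 + 3 places per block.
- **Background:** enrolment is described as under way, so the block size became public during recruitment.
- **Eligibility:** telephone screening is by study staff, who are not identified further, and providers confirm ADT history before entry. A man's stratum is therefore known before he is randomized.

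**The concern.** Central generation hides the list, but it does not hide what follows from the block structure. Once three men in a block have gone to one arm, every remaining place in that block belongs to the other arm. A constant and public block size makes this a matter of counting. With two strata and no stratification by site, there are only two sequences to follow, and the coordinator is the person told the assignments.

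At stake is concealment before randomization. Some entry criteria call for judgement, such as health conditions that might interfere with taking part, or willingness to take part fully. Baseline visits are also booked by appointment. If someone with foreknowledge of the next arm had a hand in these steps, the type of man entering each arm could be steered. The arms are visibly different (supervised group training three times a week against emailed links), so staff could hold views on who suits which.

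**Working it through.** **Inputs.** Block size 6, two ADT strata, coordinator told assignments (Randomization and interventions). Two arms (Design and settings). 125 per group, total 250 (Power and sample size calculation).

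**The plan's own figure.** The article gives no figure for predictability. Its total, used here only for scale, reproduces: 200 complete cases / (1 − 0.20) = 250.

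**Step 1: certain allocations in a 3:3 block.** There are C(6,3) = 20 equally likely orderings. An allocation is certain if one arm is already used up, so the number of certain places is the length of the final run.

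| Final run | Orderings | Probability |
|---|---|---|
| 1 | 2 × C(4,2) = 12 | 0.6 |
| 2 | 2 × C(3,1) = 6 | 0.3 |
| 3 | 2 × 1 = 2 | 0.1 |

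Mean = 1 × 0.6 + 2 × 0.3 + 3 × 0.1 = 1.5 per block, and 1.5/6 = 25%. The closed form agrees: for a block of 2m the expected number is 2m/(m + 1), which at m = 3 is 6/4 = 1.5. By position, the 4th, 5th and 6th places are certain with probability 0.10, 0.40 and 1.00. The minimum in a completed block is 1/6 = 16.7%.

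**Step 2: best-guess success.** The observer guesses the arm with more places left and tosses a coin at ties. Expected correct guesses = 3 + (64/20 − 1)/2 = 3 + 1.1 = 4.1 of 6, or 68.3%, against 50% with no information.

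**Step 3: whole trial.** 0.25 × 250 = 62.5 if every block were completed. Simulation of 250 men over two strata gives a mean of about 61.5 (24.6%), with 95% of simulated trials between 53 and 71. The result is nearly the same whether 30%, 50% or 70% of men fall in one stratum. The small shortfall comes from incomplete last blocks.

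**Step 4: random block sizes.** These are simulations with 125 men per stratum (an assumed even split) and sizes drawn with equal probability. The observer knows the set of sizes but not their order, and updates after every assignment.

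| Sizes | Certain | Best guess correct |
|---|---|---|
| 6 only | 24.5% | 68.1% |
| 4, 6 | 5.5% | 69.1% |
| 4, 6, 8 | 2.3% | 67.9% |
| 6, 8, 10 | 1.8% | 66.2% |

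Varying the sizes removes nearly all certainty. It barely changes how often an informed guess is right.

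**The case against.** A reader might infer that staff already know a quarter of the assignments, or that selection is already biased. The article supports neither.

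- **Staff knowledge.** The article does not say that staff were told the block size; publication only makes it discoverable. The 25% applies to someone who knows the size and follows assignments in order within a stratum. This stands as a limit.
- **The link to recruitment.** The coordinator is not said to screen, consent or schedule. Screening is by study staff and consent by the study team at one institution, and the article neither includes nor excludes the coordinator. This stands: the route to bias is open but not documented.
- **Timing.** By the time of randomization a man has been screened, has consented, has had his ADT history confirmed and has completed baseline, including diet recalls and a urine test 3–6 days after the creatine capsule. Which place he takes depends largely on when he finishes, so an early judgement is hard to aim at a known place. Several criteria are objective. This narrows the room for steering but does not close it, because baseline is booked by appointment.
- **Assessors.** It is tempting to add that blinded assessors could unmask men by inference within a block. They would need the block size, the stratum, the order of randomization and the arms of enough other men in the block. The article does not say that assessors see the order or block membership, so this is speculation.
- **Benefit of the remedy.** On the same simulated basis the guess rate moves only from 68.1% to 67.9% with sizes 4, 6, 8. This is correct, and the remedy should not be presented as removing predictability. What it removes is certainty.

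A fixed block size with central generation is also a common choice, and the article does not contradict itself on this point.

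**Conclusion.** The point holds as a cheap improvement to concealment; it does not identify an error in the design. A single block size of 6, published during enrolment, makes on average 25% of allocations certain (16.7% to 50% in any completed block, about 61 of 250 men overall) for an observer who knows the size and tracks the stratum. The article places the coordinator where such tracking is possible, if being informed about assignment means being told each one, which is the natural reading. The figures also assume 1:1 blocks. Selection bias remains a possible consequence only. A fuller protocol might describe further concealment, but it could not undo the publication of the size.

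**What to change.** Complete the block now open in each stratum. Then have the biostatistician generate the unused part of each list with block sizes that vary at random, for example 4, 6, 8, or 6, 8, 10. Withhold the sizes from the coordinator, recruiting staff, assessors and all study-facing documents until enrolment closes. Certain allocations among men randomized afterwards fall to about 2%, even if the set of sizes becomes known; the best-guess rate remains about 66–68%.

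The cost is a list change during the trial, to be documented under the single IRB protocol, and slightly larger possible imbalance. The largest difference between arms within a stratum is half the block size: 3 with blocks of 6, 4 if the largest block is 8, and 5 if it is 10. The change helps only future allocations, and the places left in the blocks now open stay as predictable as before. Sample size, outcomes and the planned models do not change.

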#### iLIVE intervention

The iLIVE intervention is an amalgam of previous interventions that have shown efficacy in improving diet quality and promoting weight loss, as well as increasing physical activity, especially aimed at improving strength and physical function, i.e., resistance training, among cancer survivors. The message library developed for the efficacy-proven Reach-out to Enhance Wellness (RENEW) intervention which was originally delivered via tailored print materials and telephone counseling to 641 breast, prostate and colorectal cancer survivors [41–43], was first adapted for web-use in the Daughters, dUdes, mothers and othErs Together (DUET) trial among 112 cancer survivors and chosen partners [44, 45], as well as the AiM, Plan and act on LIFestYles (AMPLIFY) trial (*n* = 351) [15, 46, 47], both of which confirmed efficacy. The web-based interventions which provide content that is refreshed routinely via tips of the day, weekly interactive sessions (tutorials), features to track dietary behaviors and body weight, and over 100 tools (e.g., meal plans, grocery lists, cooking videos) were adapted exclusively to meet the needs of prostate cancer survivors on ADT. Likewise, previous functional resistance training programs found effective in improving strength and reducing falls in supervised, facility-based group classes [48–50], were adapted to live remote instruction using standard videoconferencing software (e.g., Zoom), and led by a trained instructor who leads the exercises, modifies exercises for safety and tolerance, provides feedback on proper form, and offers encouragement. A second staff member is either online or on call during exercise sessions to assist with videoconferencing issues and/or safety monitoring. The resistance training program starts with several weeks of mobility and stability exercises designed to improve efficiency and safety of functional exercises that are the core of the functional strength training program. These mobility exercises are then integrated into the warm-up moving forward. The functional strength training program consists of a 60-minute session with a 5–10-minute warm-up, 45 min of functional resistance training, followed by a 5–10-minute cool down. The routine set of functional exercises consists of wall-sits, chair stands, step-ups, push-ups, rows, and core (e.g., plank, bird dog, bridge, dead bug) that are done during each session. As with prior facility-based programs, weighted vests are used to provide overload - an innovative method to progressively increase resistance in the lower body to improve musculoskeletal function without safety risks related to balance disruption that can occur with handheld weights. Given that the vest has multiple pockets distributed evenly around the torso with each holding a ½-lb weight, exercise intensity can be adjusted slowly and in an ergonomically efficient and safe way. The volume of resistance training progresses from the low-to-high moderate intensity range over the 24-week intervention using progression outlines in which vest weight (intensity) is gradually increased from 4% to 15% of body weight, while sets increase from 1 to 3 sets of 10–15 reps (as weight increases the rep range will decrease) [36, 48, 51]. Participants login thrice weekly, for 75-minute sessions that open 15 min prior to and after the exercise session to provide men with time and opportunity for personal interactions - a key element that provides valued peer support that can optimize adherence and retention. Social support, along with self-efficacy and reducing barriers to behavior change are key constructs of Social Cognitive Theory [39, 40], which serves as a unifying behavioral framework for both the physical activity and diet-related components of the iLIVE intervention.

#### Enhanced Usual Care (EUC)

As with men assigned to the iLIVE intervention, participants assigned to this arm receive the self-monitoring devices described above, as well as links to consensus-driven diet and exercise information in the public domain, such as American Cancer Society’s Guidelines for Cancer Survivors (https://www.cancer.org/health-care-professionals/american-cancer-society-survivorship-guidelines.html), the American College of Sports Medicine’s Moving Through Cancer (https://www.exerciseismedicine.org/eim-in-action/moving-through-cancer/) and the American Institute for Cancer Research New American Plate (https://www.aicr.org/cancer-prevention/healthy-eating/new-american-plate/). Monthly newsletters posting links to this information (identical links which are embedded within the website content that comprises the experimental iLIVE intervention) are provided to encourage trial retention, and to ensure that all trial participants receive the standard of care for lifestyle factor guidance in accordance with recommendations of the American Society of Clinical Oncology and the National Comprehensive Cancer Network [52–54].

### Statistical analysis

#### Power and sample size calculation

The sample size requirements for this RCT were based on estimates obtained from an ongoing trial [36]. We estimated that 40% of men assigned to the iLIVE intervention vs. 10% of those assigned to usual care will demonstrate clinically significant improvements from baseline to 6-month follow-up in the obese frailty phenotype (defined as clinically significant weight loss of 5% and clinically meaningful change in 2 or more frailty components, i.e., weakness, slowness, fatigue, inactivity, and/or illness). However, we powered this trial to detect smaller effects that are likely still clinically meaningful. Assuming alpha=0.05 (two-tailed) and power=0.80, a sample size of 200 complete cases (100 in each group) would be required to detect proportional differences in the 18–20% range. Assuming an attrition rate of ~ 20%, the total sample size required is *N* = 250 (*n* = 125 in each group). If attrition is lower than expected, we will need to randomize fewer participants to achieve the desired sample size. Additionally, this sample size results in even more statistical precision when examining secondary outcomes that yield continuous data.

Sample sizes for the implementation analysis are based on estimates of achieving thematic saturation [55, 56]. Here, we anticipate interviewing 30 prostate cancer survivors (6 who refuse trial participation, 12 who enroll but drop out before the end of 6 months, and 12 who complete their 6-month assessment). Maximum variation sampling will be done based on study group allocation (enrollees only), age (< 75 vs. 75+) and region of the country (west vs. east). Plans also include interviewing eight oncology clinical care team members (different types of oncology providers and nurses) and eight health system administrators (Chief Executive Officers, etc.).

#### Planned data analysis

##### Quantitative data analysis

Once data collection is complete, study retention will be examined to determine between-arm differences and explore potential differences between drop-outs and study completers. Study data will be examined using standard descriptive statistics and graphics to check for distributional assumptions, the presence of outliers, and patterns of missingness to inform final modeling strategies (e.g., the use of model-based maximum likelihood estimation) [57]. All analyses will be conducted using an intention-to-treat approach (using all data from randomized participants who are not excluded due to death or the development of other serious subsequent conditions that affect body weight and function) using R v3.3.2171 9 (R foundation, Vienna, Austria) and Mplus v7.31172 (Los Angeles, CA) software. In addition to traditional significance testing, Cohen’s d or odds ratio effect sizes (with 95% confidence intervals), as appropriate, will be estimated for change in primary and secondary endpoints across time. Model diagnostics (e.g., examining residual/predicted value plots) will be used to confirm statistical assumptions have been met. In the case of violations, more robust estimation procedures, such as nonparametric bootstrapping, will be employed as appropriate.

Standard logistic regression models will be used to test between-arm differences for both the primary and secondary binary outcomes. Complementary analyses will be conducted on each continuous frailty component separately using a linear mixed effects modeling approach implemented in the R lme4 package. Contemporary methods will be used to control for false discovery rates when testing secondary outcomes [58]. Durability of the effect of iLIVE vs. the EUC intervention after the structured program stops (i.e., at 6 months), will be explored in a limited number of outcomes (e.g., body weight, physical activity and self-reported measures of fatigue and quality of life using baseline to 12-month data). Time will be modeled either as a fixed effect with two contrasts comparing baseline to 6-month, and baseline to 12 month follow up or as a piecewise model with separate estimates of change between baseline and 6 months and 6 months and 12 months. The primary effects of interest will be the cross-level interactions between intervention group (fixed binary predictor) and the time contrasts. Significant interactions will indicate that outcome change across time differs between the intervention groups. Potential moderators (e.g., age, BMI, time from diagnosis) will be explored by adding these terms to the models and testing for interaction. These analyses will allow us to determine the characteristics of patients who have the highest likelihood of change. We also have experience using Latent Class Analysis on longitudinal change estimates to discover clusters of intervention responders [59].

